## Results

### Ethics Approval and Trial Registration

This study will meet the ethical guidelines outlined in the National Statement on Ethical Conduct in Human Research (NHMRC, ARC & UA) [58]. This study has been granted full approval from the Federation University Australia Human Research Ethics Committee (Project # A19-036) and is registered with the Australian New Zealand Clinical Trial Registry (ACTRN: ACTRN12619000705189).

### Timeline

As of June 2021, the project has not begun recruitment. The project is predicted to begin participant recruitment in the third quarter of 2021, with data collection beginning as eligible consenting participants make contact.

## Discussion

This paper describes, to our knowledge, the first study to assess an instructed mimicry task to increase emotion recognition ability in people with alexithymia and ASD. Despite the formulation of the alexithymia hypothesis, very few studies have assessed the impact of alexithymia in interventions aimed at increasing social functioning and in particular, emotion recognition. Additionally, to our knowledge, no other study has explored the benefits of instructed mimicry on emotion recognition in people with ASD and alexithymia. This mixed factor, 2x2x2, within-between design will assess the efficacy of the instructed mimicry task to increase FEER. This study design will enable the assessment of baseline and improvement scores individually for people with and without ASD while controlling for levels of alexithymia. This will allow analyses of how this intervention uniquely benefits ASD without the interference of alexithymia, which is known to frequently co-occur in ASD [9]. If this task is successful at increasing emotion recognition, it could provide easily accessible training to those with ASD, alexithymia, and other disorders that typically have high rates of alexithymia such as schizophrenia [59].

One proposed benefit of this intervention for people with alexithymia and ASD is that the software does not require supervision. This will likely benefit these populations as they typically enjoy computer-based interaction rather than social interaction, as indicated by previous studies (eg, [60]). This has the added benefit of improving access to the task as it could be used on a home computer, which may eliminate a key barrier to treatment.

Despite the benefits of this task and study design, some limitations are present. First, matching the ASD and AM groups on levels of alexithymia improves our ability to exclude alexithymia as a contributing factor of emotion recognition accuracy. Unfortunately, it also means that other confounding factors may have been systematically introduced when matching on alexithymia. This limitation will make it difficult to attribute any benefits of the intervention task specifically to autism. Additionally, when comparing emotion recognition accuracy, it will limit our ability to suggest whether emotion recognition difficulties are related to ASD or to alexithymia, as per the alexithymia hypothesis.

A second limitation is the once-off nature of this intervention. While similar tasks have shown improvement over one session (eg, [61]), it would be ideal to administer the intervention several times over a longer time period and measure in between. Given that the primary variable, emotion recognition, is measured during the task (the intervention task is the posttest), this could be done by having participants complete the task at home for a specific amount of time and intervals.

In summary, it has been suggested that emotion recognition problems in ASD are instead due to co-occurring alexithymia. This study matches an ASD and non-ASD general population group (the AM group) on alexithymia to improve the ability to detect if this is true. Further, this study design will aid in detecting if the instructed mimicry intervention benefits people specifically with ASD or if it more broadly aids people with alexithymia. If successful, this adjunct intervention will be cost-effective and easy to implement while also removing entry barriers as it could be used at home on a personal computer.

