## Methods

### Study Design

The study design is a mixed factor 2x2x2 within-between design. Participants who meet inclusion and exclusion criteria will be randomized to a control task or the experimental task. Inclusion and exclusion criteria and pretrial control variables will be collected during an online screening stage and during an in-person clinical interview. Baseline outcomes will be assessed directly before the control task or experimental task. They will then be assessed again during the control and experimental tasks. The study will conclude with a brief measure of satisfaction of the task and a debriefing session. See Multimedia Appendix 1 for a step-by-step workflow of a participant through the study.

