### Primary Outcome

The primary outcome being assessed is an increase in FEER. This will be measured by comparing the percent of correctly identified facial emotion expressions from the baseline assessment task to the instructed mimicry experimental task. Additionally, the percent of correctly identified expressions will also be compared between the control condition and the intervention condition. This will provide 2 primary metrics: before-after percent improvement and control group to experimental group percent improvement.

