### Intervention

The task will be delivered in-person at the Federation University Psychology Clinic in Ballarat, Australia, by the primary author in a small counselling room. The room will have 2 computers on a desk, each with separate monitors and peripherals (one for the participant and the other for recording eye-tracking data). Participants will take part in the task 1 participant at a time based on a mutually agreed upon time and date. Participants will only undergo this task once, and it is expected to take approximately 30 minutes based on prior testing where a small neurotypical group took approximately 25 minutes to complete the task in a usability test. The intervention is a software-based FEER training task that presents a series of different facial expressions and requires individuals to firstly mimic and then select which emotional expression they saw. The software runs on Microsoft Windows 10 and requires only minimal system requirements and a mouse.

The intervention task condition will begin with the software presenting a basic description of 6 facial expressions (fear, sadness, happiness, anger, disgust, surprise) and tips on how to spot each expression. Next, participants will be verbally advised by the experimenter and by on-screen text that a series of emotion recognition trials will begin shortly. Further, they will be told that after each emotion is displayed that they should try their best to mimic (copy) the observed facial expression with their own face. Once they have mimicked the expression, they should then use the 6 labelled buttons on the right-hand side (or associated keyboard shortcut) to choose which emotion was displayed. After selecting the answer using 1 of the 6 buttons, a 5-point Likert scale on the computer screen will ask the participant “How well did you mimic the expression?” with responses ranging from 1 “not very well” to 5 “very well.” This will repeat for each of the 36 trials. The trials will include various models of both men and women depicting the 6 emotions.

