### Statistical Analyses

The data will be analyzed using SPSS, Version 25. Alexithymia will be analyzed to aid in matching the AM group and ASD group on alexithymia. To ensure that the ASD and AM groups, and also the experimental and control groups, are comparable, means and standard deviations of participant characteristics will also be compared with tests of difference.

The study design is a mixed factor, 2x2x2, within-between design (see Table 2), and therefore, the most appropriate test of difference is a mixed factorial ANOVA, set up according to Table 2 with IQ, depression, and anxiety variables added as covariates. This will provide analyses of whether the instructed mimicry intervention task was effective by comparing baseline scores to posttest scores. Additionally, it will provide the ability to compare posttest scores between the control group and the intervention group. Finally, this analysis will have the additional ability to discern these differences based on group (ASD group and AM group).

In addition to the mixed factorial ANOVA, a hierarchical regression analysis will also be conducted (see Table 3) to determine the predictive ability of alexithymia on the primary outcome variable.

**Table 2 table2:** Experimental group and intervention design.

Time point	ASD^a^ group (n=~32)		AM^b^ group (n=~32)	
	Control task condition (n=~16)	Mimicry task condition (n=~16)	Control task condition (n=~16)	Mimicry task condition (n=~16)
Pretest	FEER^c^ task score	FEER task score	FEER task score	FEER task score
Posttest (the intervention task is the posttest)	FEER task score	FEER task score	FEER task score	FEER task score

^a^ASD: autism spectrum disorder.

^b^AM: alexithymia-matched general population.

^c^FEER: facial emotion expression recognition.

**Table 3 table3:** Hierarchal regression stages for analysis.

Stage	Variables
Stage 1	IQ, age, gender
Stage 2	+Autism
Stage 3	+Alexithymia
Stage 4	+Intervention

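### FEER is scored after randomisation only while the assigned instruction is in force, so the trial can show an immediate effect of instructed mimicry but not a training effect or a gain in ability

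*Protocol article*

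**What the plan says.** The protocol article fixes the timing of the outcome in several places, and they agree.

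- Study Design, on the outcomes after baseline: "They will then be assessed again during the control and experimental tasks".
- Statistical Analyses, Table 2, row label: "Posttest (the intervention task is the posttest".
- Discussion, on how the task could be repeated: "Given that the primary variable, emotion recognition, is measured during the task (the intervention task is the posttest".
- Measures, Table 1: FEER is marked at pretest and during the experimental task. The posttest column is blank for FEER and holds only the satisfaction questionnaire.
- Primary Outcome: the before-after metric is obtained by "comparing the percent of correctly identified facial emotion expressions from the baseline assessment task to the instructed mimicry experimental task". A second metric compares control with intervention.
- Intervention: the mimicry task "requires individuals to firstly mimic and then select which emotional expression they saw", repeated over 36 trials in a single session.
- Comparator/Control Group: baseline is the same task without the mimicry instruction. At the second assessment the control arm is told to look at the whole face before answering.

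The language about purpose goes further. The Intervention section states: "The intervention is a software-based FEER training task". Table 1 names the primary outcome as FEER ability. The Abstract's Objective asks which population benefits from the training. The Discussion adds: "If this task is successful at increasing emotion recognition, it could provide easily accessible training to those with ASD, alexithymia".

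**The concern.** Training and ability both refer to something the participant keeps after the task. The only post-randomisation FEER score is taken while the aid is being used. A higher score in the mimicry arm could arise entirely because copying a face helps the answer that follows, with nothing learned.

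The article's own rationale makes this a live possibility. Its section on facial mimicry and oxytocin reports that instructions to mimic improved recognition of the expression being mimicked, and that restricting mimicry reduced recognition. Both are described as effects on the recognition at hand.

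At stake is what a positive result may be said to mean. Read as evidence for a training tool for home use, it would go beyond what was measured. The Discussion lists the one-off session as a limitation, but treats in-task scoring as a convenience for repeated use. Repeating the task at home and scoring it the same way could show whether accuracy under instruction rises across sessions. It still would not show accuracy without the instruction.

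**Working it through.** **What each score contains.** Assume effects add, and write the change from baseline in each arm as:

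- mimicry arm: P + A_m + C_m
- control arm: P + A_c + C_c

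P is practice plus any difference between the baseline and task picture sets. A is the immediate effect of the instruction in force. C is any gain that would remain without it. P is taken as common to both arms, because the control task is described as identical apart from the instruction.

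**Between-arm contrast.** Subtracting gives D = (A_m − A_c) + (C_m − C_c). P cancels, so randomisation protects the comparison. But D is one observed quantity with two unknown parts. The split D + 0 (all immediate), 0 + D (all carry-over) and every other split fit the data equally well. Neither the mixed ANOVA nor the hierarchical regression can separate them, because no measurement contains C without A.

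**Before-after metric.** Within the mimicry arm the change is P + A_m + C_m. This is weaker still: practice and picture set no longer cancel.

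**What a further block would add.** With no instruction in either arm, the between-arm difference is C_m − C_c, provided that participants stop mimicking when no longer told to.

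**Does the sample size bear on this?** The Sample Size Calculation gives f² = 0.27, α = 0.05, power 80%, N = 58. With the six predictors of Table 3 (IQ, age, gender, autism, alexithymia, intervention) and an overall regression F test:

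- noncentrality = f² × N = 0.27 × 58 = 15.66
- degrees of freedom 6 and 58 − 6 − 1 = 51
- power = 0.808, and 58 is the smallest N reaching 0.80

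The stated 58 is reproduced. Adding 10% gives 58 × 1.10 = 63.8, or 64 as stated. The effect size is attributed to two earlier studies, one of which the article describes as testing instructions to mimic. That basis suits an in-task score. The article gives no effect size for an uninstructed score, so no sample size can be worked out for one.

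**Length of an added block.** Each trial shows a neutral face for 3 s and the expression for 0.5 s. Response time is not given; assume 5 to 10 s.

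- 36 × (3.5 + 5) = 306 s = 5.1 min
- 36 × (3.5 + 10) = 486 s = 8.1 min

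As a check, the Intervention section reports about 25 minutes in usability testing and expects about 30. If all of that were 36 trials, it would be 1,500/36 = 41.7 s to 1,800/36 = 50 s per trial. That time may include the introduction, mimicking and self-rating, and its scope is not stated. So 5 to 8 minutes may be too low.

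**The case against.** The strongest defence is that the plan is consistent with itself. The first aim, under Study Aims, concerns the efficacy of an instructed mimicry task condition against a control condition. The primary outcome, Table 2 and the Hypotheses all use in-task score minus baseline. Read narrowly, aim, outcome and hypotheses agree, and the randomised contrast answers them. Both arms are scored under an active instruction, with the control instruction chosen to match attention. The home-use remarks are conditional, and in-task scoring is disclosed more than once. Testing an immediate effect before testing retention is a legitimate choice for a first, single-session study. All of this stands, and it is why the point is limited to what may be concluded.

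A reader might go further in three ways, none of which the document supports.

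- **That the estimand misses the aim.** It does not miss the aim as worded under Study Aims. The gap is with the training and ability wording elsewhere.
- **That a null result could conceal learning because mimicking disrupts answering.** Nothing in the article suggests such interference; the studies it cites point the other way.
- **That the primary endpoint should become a repeat of the uninstructed baseline task.** Reusing the baseline pictures would bring in item memory, and replacing the endpoint would remove the stated basis for f² = 0.27.

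**Conclusion.** The point holds in a limited form. The trial can estimate the immediate effect of a mimicry instruction against an attention instruction on recognition accuracy while each is in force. It cannot estimate a carried-over gain, so it cannot support a claim of training or of improved FEER ability. The article makes or implies that claim in the Abstract's Objective, Table 1, the Intervention section and the Discussion, and its limitations do not address the gap.

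No numerical size can be given: carry-over is not identifiable from the planned data. This conclusion rests on the stated timing of the scores, not on the additive notation or the assumed response times. The hypotheses on improvement scores carry the same narrower meaning, including those on alexithymia and on the ASD comparison.

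**What to change.** **Minimum change, wording only.** Restate the primary outcome, hypotheses and conclusions as recognition accuracy during instructed mimicry compared with instructed attention. Remove the training and ability claims, including the Table 1 label and the forward-looking remarks on home training. Add to the limitations that no FEER test without an instruction follows the task. The cost is a narrower claim.

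**If a training claim is to be kept.** Add a short block after the task in both arms, with no mimicry or attention instruction. Use a further picture set matched for difficulty, not the baseline pictures. Compare the arms on it with adjustment for baseline, and declare it secondary. The in-task score stays primary, so the stated sample-size basis is untouched.

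**Cost of the block.** It uses the same software and visit, and the Timeline says recruitment had not begun. It adds roughly 5 to 8 minutes per participant under the assumed response times, possibly more, and needs one more matched picture set. It would have no stated power. It would show accuracy without the instruction, not necessarily without mimicry, since participants may go on copying faces unprompted. It would also show same-visit carry-over only, not lasting retention.

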## Appendix

Multimedia Appendix 1 Workflow of participants through in-person segments of study.

Multimedia Appendix 2 Questionnaire of Task Satisfaction.

Multimedia Appendix 3 Selection process of pictures to match task difficulty between the baseline task and the experimental task.

## Abbreviations

ADOS: Autism Diagnostic Observation Schedule
AM: alexithymia-matched general population
AMSE: Autism Mental Status Exam
ANOVA: analysis of variance
AQ-10: Autism Spectrum Quotient
ASD: autism spectrum disorder
DASS-21: Depression Anxiety Stress Scales-21
FEER: facial emotion expression recognition
K-10: Kessler Psychological Distress Scale
PCF: predictive coding framework
PP: provisional psychologist
TAS: Toronto Alexithymia Scale
WAIS-IV: Wechsler Adult Intelligence Scale - Fourth Edition
WASI-II: Wechsler Abbreviated Scale of Intelligence
WSEFEP: Warsaw Set of Emotional Facial Expression Pictures
